| Technical Support        | 
The human dental pulp mesenchymal stem cell preparations used in this project were manufactured by Beijing SH Biotechnology Co., Ltd., Beijing 100070, China, with a cell preparation workshop that meets the GMP production conditions. The preparation process of human dental pulp mesenchymal stem cell used in the study, such as isolation, culture, characterization, quality control, etc., was carried out under the guidance of the corresponding standard operation procedures (SOPs), and the three batches of MSCs used in the study with batch numbers 01012012110205D, 01012012110701D, 01012012111304D have passed strict self-inspection by the company and third-party inspection by the China Academy of Food and Drug Administration
                                                                                                                                                                                                                                                                                                                                                                                                                                                                                                                                                                                                                                                                                                                                                                                                                      |

|  |                                                                                                                                                              |
|--|--------------------------------------------------------------------------------------------------------------------------------------------------------------|
|  | (CAFDA), which are in line with the quality standard of clinical-grade stem cells, and provide safety assurance for the subjects as well as the researchers. |
|--|--------------------------------------------------------------------------------------------------------------------------------------------------------------|

| No. | Project                                                                                                                           |                                                                                                                  | Screening /treatment period |                                        | Research follow-up period |                                                           |                   |                   | Long-term follow-up |
|-----|-----------------------------------------------------------------------------------------------------------------------------------|------------------------------------------------------------------------------------------------------------------|-----------------------------|----------------------------------------|---------------------------|-----------------------------------------------------------|-------------------|-------------------|---------------------|
|     |                                                                                                                                   |                                                                                                                  | Screening period            | Treatment period                       | Follow-up visit 1         | Follow-up visit 2                                         | Follow-up visit 3 | Follow-up visit 4 | Long-term follow-up |
|     |                                                                                                                                   |                                                                                                                  | (D-14-0)                    | (D1)                                   | (D7±1) , Telephone        | (D30±3)                                                   | (D90±3)           | (D180±5)          | (D360±5)            |
| 1   | Sign ICF                                                                                                                          |                                                                                                                  | ×                           |                                        |                           |                                                           |                   |                   |                     |
| 2   | Inclusion /Exclusion Criteria                                                                                                     |                                                                                                                  | ×                           | ×                                      |                           |                                                           |                   |                   |                     |
| 3   | Demographic information                                                                                                           |                                                                                                                  | ×                           |                                        |                           |                                                           |                   |                   |                     |
| 4   | Medical history information                                                                                                       |                                                                                                                  | ×                           |                                        |                           |                                                           |                   |                   |                     |
| 5   | Vital signs: respiration, heart rate, blood pressure (systolic, diastolic), temperature (axillary), clinical condition assessment |                                                                                                                  | ×                           | × (Before / 2h±30 min after injection) |                           | × (Double DPSCs injection group 2h±30min after injection) |                   |                   |                     |
| 6   | Periodontal clinical indicators: AL, PD, BOP, GR, TM                                                                              |                                                                                                                  | ×                           | ×                                      |                           |                                                           | ×                 | ×                 | ×                   |
| 7   | Lab tests                                                                                                                         | Routine blood tests                                                                                              | ×                           | ×                                      |                           | ×                                                         | ×                 | ×                 |                     |
|     |                                                                                                                                   | Coagulation                                                                                                      | ×                           | ×                                      |                           |                                                           |                   |                   |                     |
|     |                                                                                                                                   | Liver and kidney function                                                                                        | ×                           | ×                                      |                           | ×                                                         | ×                 | ×                 |                     |
|     |                                                                                                                                   | Ultrasensitive C-reactive protein                                                                                | ×                           | × (Before / 2h±30 min after injection) |                           | × (Double DPSCs injection group 2h±30min after injection) |                   |                   |                     |
|     |                                                                                                                                   | Infectious Disease Screening: HBsAg, HBsAb, HBeAg, HBeAb, HBcAb, Anti-HCV, HIVcombin, Anti-TP, CMV-IgM, CMV-IgG. | ×                           |                                        |                           | ×                                                         | ×                 | ×                 |                     |

|    |                                                                                                    |                                                  |   |                                                   |   |                                                                 |   |   |   |
|----|----------------------------------------------------------------------------------------------------|--------------------------------------------------|---|---------------------------------------------------|---|-----------------------------------------------------------------|---|---|---|
|    |                                                                                                    | Immunology: IgA, IgG, IgM,
total IgE. | × | × (Before / 2h±30 min
after injection)         |   | × (Double DPSCs injection
group 2h±30min after
injection) | × | × | × |
|    |                                                                                                    | Pregnancy Tests                           | × | ×                                                 |   | ×                                                               | × | × |   |
|    |                                                                                                    | Urinalysis                                | × | ×                                                 |   |                                                                 |   |   |   |
| 8  | Basic periodontal treatment: Supragingival cleaning,
Subgingival scaling, root planning |                                                  | × | × (1/2 Subgingival
scraping + root
planing) |   |                                                                 |   |   |   |
| 9  | Drug delivery therapy                                                                       |                                                  |   | ×                                                 |   | × (Only phase II Double
DPSCs injection group)               |   |   |   |
| 10 | Adverse event records                                                                       |                                                  | × | ×                                                 | × | × (Double DPSCs injection
group 2h±30min after
injection) | × | × | × |
| 11 | Combined medication/treatment discipline                                                    |                                                  | × | ×                                                 | × | ×                                                               | × | × | × |
| 12 | Imaging (CBCT)                                                                              |                                                  | × |                                                   |   |                                                                 | × | × | × |
| 13 | Intraoral photography                                                                       |                                                  |   | ×                                                 |   | ×                                                               | × | × | × |

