|                           | 
1. Saline iniectio group: immediately after the completion of basic periodontal treatment Injection, therapeutic dose of 0.6mL saline / dental position / person, 10 subjects;
 
2. Single DPSCs injection group: Bilateral multi-point injection was performed on a single tooth position of the subject immediately after the completion of basic periodontal treatment ejaculation, with a therapeutic dose of <math>1 \times 10^7</math> hDP-MSC cells (saline 0.6mL suspension)/dental position/person, 10 subjects were enrolled;
 
3. Double DPSCs iniectio group: Immediately after the completion of periodontal basic treatment, bilateral multi-point injection was performed on the single tooth of the subject, and the therapeutic dose was <math>1 \times 10^7</math>hDP-MSC cells (0.6mL saline suspension)/tooth position/person. A month later, bilateral multi-point injection was performed on the single tooth of the subject again. The therapeutic dose was also <math>1 \times 10^7</math> HDP-MSC cells (0.6mL suspension of normal saline)/dental position/person, and 30 subjects were enrolled.
 
In summary, in the two stages of this study, about 33 subjects are expected to be included in the normal saline control group, about 33 subjects in the stem cell treatment group, and 30 subjects in the stem cell secondary administration group, meeting the requirements of statistical analysis.
 
(2) Design of cell therapy dose
 
According to the results of previous studies, the local cell injection cell dose is: 1107Cell / 0.6 mL / tooth position / human.
 
(3) Blind setting: This study was an open study, and only periodontal data collection personnel and image data measurement personnel were kept blind. In this study, the appearance of human dental pulp mesenchymal stem cell preparations after suspension before use was pale milky uniform suspension, and the appearance of normal saline control was colorless clear liquid, so it was impossible to implement blind method for subjects and researchers conducting local injection operations.
 |

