| Research procedure | 
(1) Screening for inclusion (D-14) : After the subjects signed the informed consent, all pre-enrollment screening examinations were conducted in the periodontal/emergency comprehensive clinic of the research institution. Subjects who met the inclusion criteria and did not meet the exclusion criteria were selected Join the group. The investigator selected the subject's proposed treatment site (single tooth position/subject).
 
(2)Periodontal primary treatment (D-14~D1) : Periodontal primary treatment includes supragingival scaling, subgingival scaling and root treatment The surface is flat. Divided into 3 times, the specific treatment steps are as follows:
 
 
■ Supragingival cleaning (D- 14) : normal saline rinse and gargle, whole mouth ultrasonic supragingival cleaning and polishing, normal saline rinse;
 
■ Subgingival scaling (D-7±1, non-therapeutic dental area) : 2% bilan anesthesia, half-mouth ultrasonic subgingival scaling, flat root surface, polishing, normal saline rinse;
 
■ Subgingival scaling (D1, including treatment area) : 2% bilan anesthesia, the other half of the mouth ultrasound subgingival scaling, root surface flat, polishing, normal saline rinse.
 
 
(3) Local injection therapy (D1) : According to the randomly assigned number, all subjects were given bilateral multi-point local injection therapy of hDP-MSC cells/normal saline immediately after the peridental foundation treatment was completed. The local injection method for the peridental defect site is: Under local anesthesia, the periodontal probe was used to determine the top position of the alveolar ridge, and the needle was injected into the bottom of the periodontal bag (in the surrounding tissue at the bottom of the periodontal bag). After the needle reached the medial periodontal membrane of the alveolar ridge and touched the junction between the bone surface and the tooth root, the multi-point interstitial injection was performed on both sides of the buccal (lip) and lingual and palatine sides with a 1ml spiral syringe. The injection time is 20-30 seconds at each point. The stop point of the injection needle is located on the tooth root surface to ensure that the injected stem cell preparation can be in the tooth root The area is clustered. Specific operations are as follows:
 
 
■ DPSCs injection group: 48 subjects. Immediately after the completion of periodontal basic treatment, the patient was given bilateral multi-point injection at a single dental position, and the therapeutic dose was <math>1 \times 10^7</math> hDP-MSC cells (0.6mL suspension of normal saline)/dental position/person.
 
■ Saline iniecton group: 48 subjects. Immediately after the completion of periodontal basic treatment, the patient was given bilateral multi-point injection at a single dental position, and the therapeutic dose was 0.6mL normal saline/dental position/person.
 
 
Local stem cell secondary injection therapy (D30±3) : Only for secondary stem cells in the second phase of this study Subjects in the administration group. At the end of a one-month follow-up, the subjects were given more hDP-MSC cells on both sides Point local injection therapy. The local injection method of periodontal defect site is the same as the first local injection treatment:
 
 
■ Double DPSCs iniecton group: After 1 month follow-up, the subjects received bilateral multi-point injection at a single dental position and the therapeutic dose It was <math>1 \times 10^7</math> HDP-MSC cells (saline 0.6mL suspension)/dental position/person.
 
 
(4) Observation (D1) : After treatment, all subjects were admitted to the periodontal/emergency comprehensive clinic 2 Hours of adverse reactions observation and safety assessment.
 
(5) Follow-up (D7±1 telephone follow-up, D30±3, D90±3, D180±5, D360±5) :
 
 
■ Post-treatment follow-up: Subjects were followed up at D7±1 (telephone follow-up), D30±3, D90±3, and D180±5 once each after discharge, and clinical safety and efficacy indexes were collected.
 
■ Long-term follow-up: After the end of treatment, D360±5 follow-up was conducted once, clinical efficacy and immunological evaluation indicators were collected, and the study was ended.
 
 |

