### **3. blinding setup:**

This was an open study and blinded to periodontal data collectors and imaging data measurers. Since the study used DPSCs preparation had the appearance of pale creamy white homogeneous suspension after re-mixing before use, and the saline had appearance of a colorless appearance, it was impossible to blind the subjects and the investigators of local injection manipulation.

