**4. verification of inclusion and exclusion criteria:** The researchers screen subjects who meet the inclusion criteria and do not meet the exclusion criteria. Comprehensive assessments are conducted for the enrolled subjects to verify if they meet all the screening and inclusion criteria.

**5. allocation of treatment/randomization numbers:** Once the researchers confirm that the subjects meet all the inclusion criteria during the screening period, they will allocate randomization numbers to the subjects based on the randomization codes provided by the statisticians. This random allocation determines the group assignment for each subject. During the baseline/treatment period, the researchers will once again confirm that the subjects meet all the inclusion criteria and inform them of their final group assignment for enrollment.

**6. study compliance management:** Once subjects receive their randomization numbers and are assigned to the researchers involved in this study, it becomes the responsibility of the researchers to track and follow up with the subjects. The researchers should diligently adhere to the study protocol and informed consent form, ensuring that the subjects fully understand the study requirements and cooperate with the research. They should also regularly remind the subjects of scheduled follow-up appointments through phone calls.

**7. compensation and reimbursement:** Subjects participating in this study will receive a fee of 300 RMB per visit as compensation for transportation expenses and loss of income. The researchers are responsible for providing this compensation in cash to the subjects at the end of each visit. If the subjects are able to complete all the scheduled visits for the study, they will receive a total of 7 compensation payments, amounting to 2100 RMB per subject.

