**In the first phase, there are 2 groups, and the therapeutic dose of stem cell preparation is as follows:**

■ **Stem cell therapy group:** A treatment dose of 0.6 mL/tooth position, the cell volume was about  $1 \times 10^7$  hDP-MSC cells/tooth position/person, and the suspension was 0.6 mL of normal saline.

■ **Normal saline control group:** a treatment dose of 0.6 mL/tooth position, normal saline 0.6 mL/tooth position/person.

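### Subject masking is called impossible only because the two liquids look different, a reason that holds for the injector but not for the subject when saline is compared with the first cell injection

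*Protocol*

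**What the plan says.** The scenario summary, research design item (3), declares an open study in which "only periodontal data collection personnel and image data measurement personnel were kept blind". It then contrasts the pale milky cell suspension with saline ("the appearance of normal saline control was colorless clear liquid") and draws its conclusion from that alone: "so it was impossible to implement blind method for subjects and researchers conducting local injection operations". Section (V), item 3 on blinding, repeats the argument: "it was impossible to blind the subjects and the investigators of local injection manipulation".

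Section (9) Subject management, item 5, has the researchers re-confirm eligibility in the baseline/treatment period and then "inform them of their final group assignment for enrollment". The D1 step in section (V), item 4, mentions telling subjects only which tooth will be treated, not their group.

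The procedure itself is common to the arms. The scenario summary, research procedure item (3), says "all subjects were given bilateral multi-point local injection therapy of hDP-MSC cells/normal saline immediately after" the basic periodontal treatment. Only the double-injection arm of the second phase has another injection, at D30, and no sham is given to the others.

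**The concern.** A visible difference between two liquids unmasks a person who looks at them. The operator has to; a patient receiving an injection inside the mouth under local anaesthesia does not. So the stated impossibility does not follow from the stated reason, and the disclosure in section (9) would end any masking regardless of how the liquids look.

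Five things are at stake:

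- **Drop-out.** After treatment, the first periodontal measurement in the visit schedule is at D90. The full analysis set needs at least one efficacy assessment, and section (16), item 1, allows subjects who withdraw early to be replaced. Subjects who leave because they know they had saline can therefore drop out of the main analysis and be refilled.
- **Co-treatment and hygiene.** Over 12 months, subjects who know their arm may change home care or seek other dental treatment.
- **Adverse-event reporting.** Gum swelling and pain in the first week count as a treatment-related event. The D7 contact is by telephone, and subjects answer it knowing their arm.
- **Assessor masking.** An informed subject can tell the masked examiner the group at D90, D180 or D360.
- **Joint objective.** Safety stands beside efficacy in the study objectives, so the reporting route is not a side issue.

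**Working it through.** **1. What can the subject notice at D1?**

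| Feature | Saline | First cell injection | Place in protocol |
|---|---|---|---|
| Volume | "normal saline 0.6 mL/tooth position/person" | "and the suspension was 0.6 mL of normal saline" | Section (12), item 2 |
| Sites | bilateral, multi-point, one tooth | same | Section (12), item 3; scenario summary |
| Anaesthesia | local | same | same |
| Syringe | 1 mL | same | same |
| Time per point | 20 to 30 s | same | same |
| Appearance | clear | milky | Blinding items |

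Appearance is the only row that differs. The cells are allogeneic and prepared off site (section (12), item 1), so no tissue harvest reveals the arm.

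**2. How many subjects does this concern?** Planned numbers are in the scenario summary and section (8). (Some other places give different arm sizes; I use 33/33/30, which is repeated and adds to 96.)

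- Saline: 23 + 10 = 33
- Single injection: 23 + 10 = 33
- Double injection: 30
- Total: 33 + 33 + 30 = 96
- Could be masked throughout as to saline or cells: 33 + 33 = 66, and 66/96 = 68.8%
- Could be masked up to D30, including the D7 call: all 96

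**3. What happens at D30?** The 30 double-arm subjects learn their arm, before the D90 primary endpoint. The other 20 second-phase subjects can infer that they are not in the double arm. For them the chance of having had saline moves from 10/50 = 20% to 10/20 = 50%; they still do not know which of the two it was.

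**4. Illustration of size.** The protocol gives no awareness effect, and section (8) gives no SD or difference, so any error rate rests on an assumption. Suppose awareness shifts the mean difference by b SD at 33 v 33, two-sided 5% test:

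error = 1 − Φ(1.96 − b/√(2/33)) + Φ(−1.96 − b/√(2/33)), with √(2/33) = 0.246

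- b = 0.1: b/0.246 = 0.41, error about 7%
- b = 0.3: b/0.246 = 1.22, error about 23%

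This is a two-group normal approximation, whereas the protocol's between-group test is ANOVA or Kruskal-Wallis. It shows sensitivity to an assumption; it does not estimate a bias in this trial.

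**The case against.** The strongest reply is that this is a declared open, exploratory trial whose main outcomes are protected. Attachment level by Florida probe at D90 and the CBCT measures are read by masked staff, and none is patient-reported. That stands, and it limits the loss to the indirect routes.

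Masking would also serve one contrast only. Double versus saline and double versus single stay open from D30, as does the three-group comparison, and two masked arms beside one aware arm create a difference in expectation of their own. That stands too and must be stated in the protocol.

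Timing matters as well. Version 7.0 is dated 16 July 2021 and the extended study ends in August 2022. With follow-up to D360, injections would have to finish by about the end of August 2021. An edit therefore reaches few new subjects.

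That an opaque sleeve suits divided delivery of 0.6 mL is a practical judgement. If the operator must read the barrel, keeping the syringe out of the subject's view does the same job. Nor does the fix mask the investigator who judges whether an event is related.

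A reader might infer three stronger things that the documents do not support:

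- That the false-positive rate is inflated by a known amount. No shift is given and its direction is unknown: better home care or other treatment in the saline arm would pull the comparison toward no difference.
- That disclosure comes before the injection. Section (9) places it in the baseline/treatment period without saying so.
- That the whole trial could have been subject-masked. Without a sham at D30 it could not.

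**Conclusion.** The stated impossibility is unsupported for subjects in the comparison of saline with a single cell injection. It is supported for the injector. The protection given up is partial: 66 of 96 planned subjects throughout and all 96 up to D30, against arm-aware drop-out, co-treatment, hygiene changes, adverse-event reporting and disclosure to the examiner. It does not invalidate the primary endpoint, because that is read by masked staff. The conclusion assumes the 33/33/30 plan and that the subject can be kept from seeing the barrel, which nothing in the protocol contradicts. The range of about 7% to 23% is illustrative only. The point is worth correcting, at moderate weight.

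**What to change.** In the scenario summary (blind setting) and section (V), item 3, replace the claim of impossibility with text to this effect: the injector is unmasked; subjects are not told whether they received saline or cells; the syringe is covered by an opaque sleeve or kept out of the subject's view.

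In section (9), item 5, delete the disclosure of group. Disclose after D360, or earlier if safety requires, and match the consent wording.

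Describe the trial as assessor-masked, and as subject-masked only for saline versus single injection among subjects not already told. State that all arms can be masked up to D30, that the double arm becomes aware then, before D90, that the other second-phase subjects learn only that they are not in it, and that contrasts with the double arm are open.

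The cost is a sleeve, one line in the injection procedure and a consent change. No dose, schedule, endpoint or sample size is touched. The downside is that subjects wait until study end to learn their group. Subjects already told cannot be re-masked; for them, the change corrects the description only.
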